## Methods/design

### Study setting

We are conducting the study in a large urban, federally qualified health center (FQHC) in Los Angeles that serves approximately 20,000 patients annually. The study is taking place at the FQHC’s two largest sites. We elected to hold the study in an FQHC because of the expected influx of patients into publicly funded clinics due to expanded coverage, an increased funding and an increase in the number of clinics due to the Patient Protection and Affordable Care Act (PPACA) [57], and the greater opportunity to reach more individuals who need treatment. The clinic currently has integrated mental health services and provides treatment for anxiety and depressive disorders; however, prior to the study, the clinic did not conduct any screening or treatment for SUD. If substance misuse was identified, patients were sometimes, but not systematically, referred to specialty care.

### Conceptual framework

In our conceptual framework, illustrated in Figure 1, the organizational readiness intervention increases provider readiness to use each of the EBP for OAUD (the two medications and the MI-based behavioral therapy) as well as readiness to adopt ICC (the service delivery intervention) to deliver the three EBP. The organizational readiness intervention consists of well-studied “implementation” tools, designed to increase the readiness of an organization to implement and deliver new practices. Our measures of organizational readiness are provider acceptability of the EBP, provider perceptions of EBP appropriateness and feasibility, and provider intention to adopt each EBP. In addition, because an aspect of organizational readiness is the ability of providers to visualize how the new practices can be adopted and integrated into the existing workflow [33], a final measure of readiness is the development of locally tailored EBP protocols and an ICC protocol that shows how the EBP will fit into clinic workflow.

**Figure 1 Fig1:**
[figure not shown]
SUMMIT conceptual framework for integrating SUD EBP into primary care.

In the second part of the conceptual framework, the service delivery intervention (ICC) facilitates the uptake of the EBP and affects service system outcomes (e.g., patient-centered SUD care, measured at the level of the patient and provider, and service utilization, measured at the level of the patient) and patient functioning outcomes (e.g., substance use, consequences of use, both measured at the level of the patient). While organizational readiness may improve immediately following the organizational readiness intervention, we expect that once the three EBP are implemented through ICC and the staff sees improved patient outcomes, a feedback loop will occur, leading to even greater staff acceptance of the new practices.

### Study design

The study is designed to test the combined effect of both an organizational readiness intervention (which includes a 1-year organizational preparation period and an 8-month pilot of the ICC condition study) and a service delivery intervention (see Figure 2). We examine the effects of the interventions on organizational readiness, service system, and patient outcomes, all of which are believed to be important in understanding the uptake of new practices [58]. To test the unique effects of the organizational readiness intervention on provider outcomes, we use a pre-post-intervention design and measure these outcomes at the beginning of the study and then again at the end of year 1. At the end of year 1, we implement an eight-month pilot test of ICC. During the pilot test, providers gain experience with the protocols, and the protocols are iteratively adapted and refined based on provider feedback. Because we hypothesize that readiness outcomes may continue to improve as providers gain experience with ICC and the three treatments, we continue to measure organizational readiness outcomes annually at years 2–5. Thus, changes in outcomes between year 1 and years 2–5 reflect the combined effect of both the organizational readiness intervention and ICC on provider outcomes. To test the effects of the interventions on service system and patient-level outcomes, we are conducting an RCT to compare the effects of ICC with SAU. Service-system outcomes are patient-centered collaborative care, utilization of SUD treatment, patient utilization of health care services, provider adoption of EBP, and sustainability of EBP. Patient-level outcomes include substance use, consequences of use, physical and mental health functioning, and patient satisfaction with SUD care.

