To address the need for change at two levels—organizational and service delivery system—to increase the intent and ability of primary care providers to identify and treat opioid and alcohol use disorders (OAUD), we designed a multi-level study to create and evaluate change at both levels. We call this study substance use motivation medication integrated treatment (SUMMIT) and focus on alcohol and opiate use disorders because of their relevance to the clinic population and availability of effective medications. At the organizational level, we test the effects of an organizational readiness intervention on the organization’s readiness to identify and treat individuals with opioid and alcohol use disorders. At the service delivery system level, we use Wagner’s Chronic Care Model [34] to reorganize and guide how care for OAUD is provided and supported; we call the service delivery intervention integrated collaborative care (ICC). Integrated, collaborative approaches have been successful in improving outcomes for patients experiencing a variety of different chronic illnesses, including diabetes [35], asthma [35], and depression [36]. ICC has improved implementation of evidence-based treatments and quality of care [37], lowered costs [38], improved patient outcomes [39-42], and is thought to be feasible for and sustainable in primary care clinics [43]. We test the effects of the organizational readiness intervention using a repeated measures pre-post design and the impact of the service delivery intervention on patient-level outcomes using a randomized controlled trial (RCT) to compare the service delivery intervention (ICC) with “service as usual” (SAU) on service system and patient outcomes. We hypothesize that provider (providers include administrators, medical and mental health providers, and other staff) readiness to implement the EBP and patient-centered SUD care will improve from the pre-organizational readiness intervention period (year 1) to the post-readiness intervention periods (years 2–5); that patients in the ICC condition will report more integrated, patient-centered evidence-based care for their opioid and/or alcohol use disorders, will be more likely to receive OAUD care, and will have lower overall health care utilization (e.g., emergency department and medical visits) than patients in the SAU condition; and that provider adoption of EBP will increase from year 2 to years 3 and 4 and that providers will still be delivering OAUD EBP a year after completion of the study in year 5. We also hypothesize that patients in the ICC condition will report less substance use, fewer SUD consequences, higher health and mental health functioning, and greater satisfaction with their SUD care 6 months after enrollment than SAU patients.

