### Interventions

#### Organizational readiness intervention

To create organizational readiness to provide evidence-based treatment for OAUD, we employ multiple tools and activities known to facilitate adoption of EBP as follows: (1) engaging (and obtaining buy-in from) key administrators through regular administrator and board briefings about the proposed study and how to best prepare the organization to implement the ICC intervention and providers to adopt the EBP [29,62]; (2) convening an implementation team that includes key clinical leadership to develop the ICC service delivery intervention and EBP protocols that fit the clinic [29,63]; (3) selecting and training physician and therapist champions to serve as role models for adopting the EBPs [29]; (4) providing trainings for the staff and providers on the ICC intervention and evidence-based treatment for opioid and alcohol use disorders [64,65]; and (5) preparing the clinic environment to identify patients with SUD by instituting universal screening and brief intervention procedures. After preparing the organization, we then conduct the final part of the organizational readiness intervention—piloting the EBP and ICC protocols and making iterative adaptations using plan-do-study-act (PDSA) cycles [66,67]. PDSA cycles offer a structured approach to engaging staff in making iterative, feedback-based changes in service delivery [65,66].

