
##### Analysis plan

The semi-structured interview and focus group data will be analyzed to identify key facilitators and barriers to implementation using classic content analyses. Our quantitative analysis of survey items will consist of pre-post, one-way repeated measures ANOVA comparisons of survey responses between pre- and all post-intervention periods.

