## Discussion

The present study responds to several critical gaps in health care services for people with SUD—the need for greater access to SUD treatment, the need for more evidence to support the growing emphasis on collaborative, integrated care for SUD in primary care settings, and the call for broader dissemination and adoption of evidence-based treatments for SUD in general and in medical settings in particular. To meet these diverse and complex needs, we designed a multi-level study that (1) combines well-studied implementation tools into an intervention to increase organizational readiness to adopt and sustain SUD EBPs in primary care and (2) tests the effectiveness of a service delivery intervention (ICC) on service system and patient outcomes related to SUD services.

Our hybrid type 2 design [59] allows us to support and study important organizational changes thought to be critical for the adoption and sustainability of new practices and to add what we believe is a necessary component of integrating SUD EBP into primary care—a service delivery intervention tailored to meet clinic specifications and the complex needs of patients with SUD treated in these settings. The study’s unique design takes into account the complexity of introducing new EBPs into a clinical setting, the barriers to integrating SUD EBP into primary care, and the chronic nature of SUD and the corresponding complex needs of SUD patients. We believe that our 18-month organizational readiness phase, starting with preparing the organization for SUD EBP delivery and ending with a pilot phase to ensure that the ICC intervention (i.e., service delivery system intervention) and EBP protocols fit the environment will ensure greater organizational readiness and thus greater likelihood of adoption and sustainability. We believe our multi-level approach—addressing organizational change plus SUD-specific service delivery—is necessary for adoption and sustainability of SUD EBP in primary care. The organizational readiness outcomes will allow us to assess whether our organizational readiness intervention improves provider perceptions of and intention to adopt the EBP while the service delivery intervention will help determine whether the ICC delivery system improves quality of care and patient outcomes compared to service delivery as usual.

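### The contrast said to isolate the readiness intervention ends before that intervention's pilot begins, and year 1 is labelled pre in one section and post in another

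*Protocol article*

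**What the plan says.** All references are to the protocol article.

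- **What the readiness intervention contains.** Study design says that it includes "a 1-year organizational preparation period and an 8-month pilot of the ICC condition study". The Organizational readiness intervention section under Interventions agrees. After the preparation activities it says "we then conduct the final part of the organizational readiness intervention—piloting the EBP and ICC protocols".
- **The contrast for readiness alone.** To test the unique effects of readiness on provider outcomes, Study design will "measure these outcomes at the beginning of the study and then again at the end of year 1". The next sentence of that section starts the pilot at the end of year 1.
- **The combined contrast.** Study design then continues the readiness measurements annually in years 2–5. It credits change from year 1 to those years jointly to readiness and ICC.
- **The hypothesis.** The Background expects provider readiness to improve "from the pre-organizational readiness intervention period (year 1", to quote as far as the open bracket. Years 2–5 are the post-readiness periods.
- **The analysis.** The readiness Analysis plan is a one-way repeated measures ANOVA of "survey responses between pre- and all post-intervention periods". The service delivery Analysis plan repeats this for provider survey items and administrative data.
- **The length of the phase.** The Discussion states: "We believe that our 18-month organizational readiness phase". It describes that phase as ending with the pilot.

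**The concern.** A pre-post contrast estimates whatever happened between its two waves. Here the label attached to the first contrast names an intervention that is still incomplete at its second wave. A result from it would be reported as the effect of the whole readiness package when it reflects the preparation year only.

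The second problem is the role of year 1. The preparation activities occupy that year, so year 1 as a whole is not a pre-intervention period. Study design treats its end as a post measurement, while the Background treats the year as pre. The text does not say which of the two year-1 surveys is the reference for the hypothesis and the combined contrast. One choice keeps the preparation-year gain and the other subtracts it out. Readiness is the implementation half of this hybrid design, so the choice bears on what that half can conclude.

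**Working it through.** No sample size, power or alpha figure is involved. The check is a timeline and a breakdown of each contrast.

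**Timeline, from Study design**

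- Month 0: first survey.
- Months 0–12: preparation.
- Month 12: second survey, and start of the pilot.
- Months 12–20: pilot.
- Years 2–5: annual surveys.

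**Share delivered at the second survey**

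- Readiness months: 12 / (12 + 8) = 12/20 = 60%. On the Discussion's 18 months, 12/18 = 67%.
- Pilot months: 0 of 8.

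These are shares of calendar time, not of effect.

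**What each contrast contains**

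Let P be the preparation-year effect, L the pilot effect, I the effect of later experience with ICC, T1 the secular change in months 0–12, and T2 the secular change after month 12. For simplicity, assume that effects add and persist, and that the surveys in years 2–5 follow the pilot.

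| Contrast | Label requires | Contrast contains | Gap |
|---|---|---|---|
| Start of study to end of year 1 | P + L | P + T1 | L missing, T1 added |
| Year 1 to years 2–5, reference = end of year 1 | P + L + I | L + I + T2 | P missing, T2 added |
| Year 1 to years 2–5, reference = start of study | P + L + I | P + L + I + T1 + T2 | secular change only |

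The first row does not depend on any reading of the term year 1. The second and third rows show that the fault in the combined contrast does.

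**Would a later post wave rescue the first contrast?** A wave after the pilot would add L. But the pilot is a pilot of ICC itself, so that wave would mix readiness with exposure to ICC. A unique effect of the full readiness package cannot be separated from ICC by moving the survey.

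**Length of the phase.** Study design gives 12 + 8 = 20 months and the Discussion gives 18. Month 12 falls before the end either way, so no contrast changes.

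**The case against.** The strongest reply concerns year 1. The Background names no survey, and the start-of-study survey is a sensible pre wave. The combined-effect label fits only that choice, which is some evidence that it was meant. A reader might infer that the hypothesis definitely takes the end-of-year-1 survey as pre, so that the preparation-year gain is certainly lost. The text does not support that. It does lean that way in Study design, which separates the beginning of the study from the end of year 1 before moving on to years 2–5. But if the start-of-study survey is meant, the end-of-year-1 survey is neither pre nor among the hypothesis's post periods, although Study design uses it as post. Figure 2, the timeline, is not shown and may date the waves. It could not change the wording of the first contrast.

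Other replies, and what stands of them:

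- **Measuring before the pilot is defensible**, because that is the last wave before exposure to ICC. This is right, and it is a reason to keep the wave. The fault is in the label.
- **Coding waves belongs in the analysis plan.** Agreed for the detail. The point here is a stated label that conflicts with a stated definition, and two stated roles for the same year.
- **The limitations already concede non-separability.** The Discussion disclaims the unique contribution of either intervention to implementation, sustainability and patient outcomes. Since the article counts intention to adopt as an implementation outcome, this can be read as reaching some readiness measures. It does not expressly withdraw the claim for provider readiness, and the Discussion still says these outcomes will show whether the readiness intervention improves provider perceptions and intention to adopt.

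**Conclusion.** The point holds in two parts of different strength.

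1. **Unconditional.** The contrast from start of study to end of year 1 does not estimate the effect of the readiness intervention as the article defines it. It omits the whole 8-month pilot and estimates the preparation year plus any secular change.
2. **Conditional.** The contrast from year 1 to years 2–5 loses the preparation-year gain only if its reference is the end-of-year-1 survey. With the start-of-study survey it matches its label apart from secular change. The conflict over whether year 1 is pre or post stands in the text either way.

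The documents give no expected size of change for any readiness measure, so the resulting bias cannot be stated in outcome units. A reader might also infer that the trial's randomized results are affected. They are not: this concerns the uncontrolled staff component, and the comparison of ICC with service as usual in patients does not use these waves. The mismatch of 18 and 20 months is a secondary inconsistency.

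**What to change.** - Name the start-of-study survey as the only pre wave for the Background hypothesis and for the combined-effect contrast, and correct the year-1 label in the Background.
- Relabel start of study to end of year 1 as the change over the preparation year before the pilot, and drop the claim that it is the unique effect of the whole readiness intervention.
- Label start of study to years 2–5 as the combined change with readiness and ICC.
- Label end of year 1 to years 2–5 as the added change with the pilot and ICC.
- State that all three are uncontrolled pre-post changes that include secular change.
- Carry the same wave definitions into both Analysis plan sections, before the data are analysed.
- Reconcile the 18-month phase in the Discussion with the 12 + 8 = 20 months in Study design.

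The cost is wording and contrast definitions only, since the surveys are already planned. The downside is a narrower claim about what readiness achieved on its own.

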## Abstract

**Background:**

Millions of people who need treatment for substance use disorders (SUD) do not receive it. Evidence-based practices for treating SUD exist, and some are appropriate for delivery outside of specialty care settings. Primary care is an opportune setting in which to deliver SUD treatment because many individuals see their primary care providers at least once a year. Further, the Patient Protection and Affordable Care Act (PPACA) increases coverage for SUD treatment and is increasing the number of individuals seeking primary care services. In this article, we present the protocol for a study testing the effects of an organizational readiness and service delivery intervention on increasing the uptake of SUD treatment in primary care and on patient outcomes.

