However, despite the potential benefits of providing SUD screening and treatment in primary care and the existence of evidence-based practices (EBP) suitable for delivery in these settings [13-21], uptake of evidence-based SUD treatments in primary care has been slow. Accordingly, patients are unlikely to receive treatment for their SUD in primary care [20-24]. Some of the organizational barriers to providing SUD treatment in primary care settings include lack of insurance reimbursement, perceived lack of time to fully assess and discuss substance use, and lack of administrative buy-in for integrating SUD care into medical practices [25,26]. At the physician level, perceived barriers to SUD treatment adoption include negative attitudes toward people with SUD, lack of confidence among physicians in their ability to treat SUDs, lack of adequate role models and access to decision support consultants, and deficiencies in training and expertise in addiction treatment [13,25-28].

Research on introducing new practices into health care and other organizations suggests that intervention at both the organizational level (i.e., to increase organizational readiness to adopt new practices) and service delivery system level (i.e., reorganizing how care is provided to support the new practice) may both be necessary to integrate and sustain EBP [29-31]. Organizational readiness refers to “the extent to which organizational members are psychologically and behaviorally prepared to implement organizational change” [32]. Interventions that increase an organization’s commitment to change and the ability of the members of the organization to visualize how the new practice could be adopted and incorporated into existing practices are both important to increasing organizational readiness and adoption of EBP [33]. However, even when an organization exhibits high organizational readiness, change may not be successful unless attention is paid to how the new practice is supported and integrated into existing care practices. Further, adapting new practices to fit the nuances of a setting is a key component of whether the practice is ultimately accepted and adopted. As Damschroder et al. note, “without adaptation, interventions usually come to a setting as a poor fit, resisted by individuals who will be affected by the intervention, and requiring an active process to engage individuals in order to accomplish implementation [30].”

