### Study participants

#### Organizational readiness intervention

Organizational readiness intervention participants are full-time clinic administrators, medical and mental health providers, and other clinic staff, including medical assistants, discharge coordinators, and front desk and security staff who agree to participate in interviews, focus groups and/or surveys (*N* = 70).

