##### Analysis plan

Our quantitative analysis of provider survey items and administrative data related to service system outcomes will consist of pre-post, one-way repeated measures ANOVA comparisons of survey responses between pre- and all post-intervention periods. To analyze patient-level outcomes, we use an intent-to-treat approach. We will first conduct a bivariate analysis to estimate the uncontrolled association between being in the ICC group and outcome. In addition, even though our design randomly assigns patients, we will assess any possible imbalance in covariates between ICC and SAU groups including age, gender, race/ethnicity, and education that affect the impact of the ICC intervention on the outcomes. In cases where observed imbalances are attributable to sample attrition, we will correct for potential bias due to attrition at follow-up using response weights. In addition, characteristics related to an outcome at a conservative significance level of α = 0.2 will be considered covariates in a multivariate analysis for reduction of bias if imbalanced or for efficiency gains. For the multivariate analyses, we will infer about the impact of ICC on an outcome by fitting hierarchical models using SAS Proc Mixed, R LME4, and Winbugs. These models take into account the multi-level structure of the data: two repeated measures over time (baseline and 6 months) nested within patient and patients nested within clinics. Sensitivity analyses will be conducted testing model functional forms, the covariates to be used, and the impact of influential outliers in the analyses results. For outcomes assessed only at month 6 (e.g., treatment satisfaction), we will use cross-sectional analyses (such as linear and logistic regression) to estimate the effect of ICC relative to SAU. This study was designed to estimate sufficient effect sizes that can be detected with a power of at least 80% when comparing the outcomes of patients randomly assigned to the two conditions in an end-status analysis at month 6 for a 5% significance level. For continuous outcomes, the study will be able to detect effect sizes of about 0.30–0.32 standard deviations. These are the kind of effects that can be expected for an intervention like ICC [42]. For dichotomous outcomes, we will be able to detect a difference of 13–14 percentage points under the assumption that the SAU group has a 15% rate of receiving the outcome.

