Despite the study’s strengths, there are some limitations. One limitation is the lack of provider randomization to test the effects of ICC on provider outcomes. This was determined to be infeasible, due to potential contamination across study conditions and lack of provider and patient support for asking patients to switch providers to match their study condition. Additionally, because we are testing the combined impact of the organizational readiness intervention with the ICC intervention, we will not be able to draw conclusions about the unique contribution of either intervention on EBP implementation, sustainability, or patient outcomes. Moreover, both the organizational readiness and the ICC interventions are complex, containing multiple elements. We will be unable to tease apart the impact of particular elements of the interventions (e.g., the effect of the decision support system from the self-management support) on outcomes. Given the emphasis on examining two complex interventions simultaneously, we elected to examine them initially in one FQHC serving a diverse population in a large metropolitan area in California. It is important to note that this occurred during a time of rapid health care reform especially in California, a state that was an early adopter of Medicaid expansion. We will not know whether our study results will be applicable to other FQHCs or in other geographical locations.

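### Uncontrolled pre-post changes in provider readiness are stated to be the effect of the interventions, although the article itself describes health care reform under way at the same time

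*Protocol article*

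**What the plan says.** The Study design section sets out two contrasts for provider outcomes.

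- **Within year 1**, from the start of the study to the end of the year: "To test the unique effects of the organizational readiness intervention on provider outcomes, we use a pre-post-intervention design".
- **From year 1 to the later years**, with readiness measured annually: "changes in outcomes between year 1 and years 2–5 reflect the combined effect of both the organizational readiness intervention and ICC on provider outcomes".

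The Analysis plan for the organizational readiness intervention specifies "pre-post, one-way repeated measures ANOVA comparisons of survey responses between pre- and all post-intervention periods". The Analysis plan for the service delivery intervention uses the same method more widely: "Our quantitative analysis of provider survey items and administrative data related to service system outcomes will consist of pre-post, one-way repeated measures ANOVA".

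The participants are staff of a single federally qualified health center, described under Study participants as including "front desk and security staff who agree to participate in interviews, focus groups and/or surveys (*N* = 70").

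On events outside the study, the Abstract says that the Affordable Care Act "increases coverage for SUD treatment and is increasing the number of individuals seeking primary care services". Study setting adds expanded coverage, increased funding and an expected influx of patients into publicly funded clinics. The Discussion says of the study that "this occurred during a time of rapid health care reform especially in California, a state that was an early adopter of Medicaid expansion".

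**The concern.** All providers are exposed to the readiness intervention, and ICC then runs in the same clinic. Time since the start of the study and exposure to the interventions therefore move together. A change in acceptability, appropriateness, feasibility or intention to adopt contains the intervention effect plus whatever else altered staff views in those years.

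The article gives concrete reason to expect other influences. It describes reform that was changing coverage, funding and demand for primary care. It also lists obstacles to treating substance use in primary care that reform could touch: "Some of the organizational barriers to providing SUD treatment in primary care settings include lack of insurance reimbursement", with perceived lack of time in the same sentence.

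At stake is the readiness hypothesis, which predicts improvement from the pre-intervention period to years 2–5. Under the Study design wording, an observed improvement would be reported as the effect of the interventions, and a null or adverse change as their failure. The design supports neither reading.

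**Working it through.** The article states no figure on this point, so the check is mainly a comparison of its sections.

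**1. Is there a control for provider outcomes?** No. Study design describes a pre-post comparison. Randomization is of patients, and the Discussion confirms that providers were not randomized. One health center takes part, and no comparison clinic is described.

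**2. Can a background trend be estimated from the pre-period?** No. Readiness is measured once before the intervention, at the beginning of the study. A single point gives no slope.

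**3. Does the analysis supply what the design lacks?** No. In a one-way repeated measures ANOVA, time is the only factor. It tests whether means differ between waves. It has no term that distinguishes calendar change from intervention change, and with steps 1 and 2 none could be identified.

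**4. Does the article describe concurrent change?** Yes: coverage (Abstract, Study setting), funding (Study setting), demand (Abstract, Study setting) and rapid reform during the study (Discussion).

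**5. Is the attribution qualified anywhere?** Not on this point. The Discussion makes three related admissions:
- Providers were not randomized, for reasons of contamination and feasibility.
- The two interventions cannot be separated from each other.
- The reform period limits applicability to other centers and places.

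Being unable to separate two interventions from each other is a different limitation from being unable to separate both of them from background change. The second is not stated.

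**6. Can the direction be fixed?** No. Wider coverage might ease a financial barrier and raise readiness. Rising demand might worsen perceived lack of time and lower it.

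**7. How sensitive is the planned test to drift?** This is an illustration only. Assume no intervention effect, a true background drift of *s* standard deviations, *n* complete pairs and within-person correlation ρ. With a paired two-point normal approximation at two-sided 5%:

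SE = √(2(1 − ρ)/n), and P(significant) = 1 − Φ(1.96 − s/SE) + Φ(−1.96 − s/SE).

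For n = 70 and ρ = 0.5, SE = √(1/70) = 0.1195. For n = 35 and ρ = 0.5, SE = √(1/35) = 0.169.

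| n pairs | ρ | s = 0.1 | s = 0.2 | s = 0.3 | s = 0.5 |
|---|---|---|---|---|---|
| 70 | 0.3 | 11% | 29% | 56% | 94% |
| 70 | 0.5 | 13% | 39% | 71% | 99% |
| 70 | 0.7 | 19% | 58% | 90% | >99% |
| 35 | 0.3 | 8% | 17% | 32% | 71% |
| 35 | 0.5 | 9% | 22% | 43% | 84% |
| 35 | 0.7 | 12% | 33% | 63% | 97% |

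Drift, correlation and number of pairs are all assumptions. The article's 70 counts staff in interviews, focus groups and/or surveys, so complete survey pairs may be fewer; 35 is an arbitrary half. The planned ANOVA over several waves would give somewhat different values. The table shows that a moderate drift could produce a significant result with no intervention effect. It does not show that such a drift occurred.

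**The case against.** **Largely disclosed already.** The limitations name the lack of provider randomization, explain it, and mention reform. Focus groups and interviews also explore facilitators and barriers, which gives some evidence on why readiness changed. This stands in part and lowers the weight of the point. But the disclosures are never joined: reform is not named as an explanation for provider changes, and the Study design statement is left unqualified.

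**The sentence only separates two contrasts.** It may be meant to distinguish readiness alone (year 1) from readiness plus ICC (later years). That is a fair account of its purpose. As written, it still assigns the whole change to the interventions.

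**Many readiness items are specific to this clinic.** Ease of prescribing a named medication here, or the fit of ICC with one's way of working, may respond little to insurance reform. That is plausible and may make the bias small for those items, but the design cannot show it.

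A reader might also infer more than the document supports:

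- *That reimbursement was changing.* The article lists lack of reimbursement as a barrier. It says that coverage, funding and demand were changing, not reimbursement.
- *That the bias favors the hypothesis.* Rising demand could act in the opposite direction.
- *That the quoted sentence also covers adoption of the practices.* Its context is the readiness outcomes. Adoption is classed as a service system outcome, and its hypothesis compares year 2 with years 3 and 4. It shares the uncontrolled pre-post analysis, but not this attribution.
- *That the trial's patient results are compromised.* ICC and usual care are compared in concurrently randomized patients, so change over calendar time affects both arms.

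**Conclusion.** The point holds for provider readiness outcomes. The Study design section claims a causal effect, combined for years 2–5 and unique for year 1, that a single-group comparison with one pre-intervention measurement in one center cannot support. The article itself describes concurrent change that could bear on the same outcomes. The limitations section comes close to saying so but does not withdraw or qualify the claim.

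No size can be put on the bias, and its sign is unknown. The probabilities in the table rest wholly on assumed drift, correlation and number of pairs, and should not be cited as an estimate. The conclusion rests on the stated design and analysis, not on those figures.

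The provider and administrative pre-post comparisons in the service delivery Analysis plan have the same limit on interpretation. The randomized patient comparison does not.

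**What to change.** 1. **Study design.** Replace the two attributions. Suggested wording: *Changes in provider outcomes during year 1, and between year 1 and years 2–5, describe change over time during the interventions and concurrent health care reform; without a comparison group they do not isolate the effect of the interventions.*
2. **Discussion, limitations.** Name concurrent reform as a rival explanation for provider changes, beside the existing remark on applicability elsewhere.
3. **Both Analysis plan sections.** State that the repeated measures ANOVA of the readiness surveys, and the pre-post comparisons of provider survey and administrative data, are interpreted as descriptive of change over time.

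A segmented time-series model is not recommended as the remedy. Before the study the clinic did no screening or treatment for substance use, so the earlier series would sit at or near zero. Universal screening is itself part of the readiness intervention, and such a model cannot address annual surveys.

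The changes need no new data and no new analysis. The cost is a weaker, non-causal claim for provider outcomes.
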